#### Qualitative

After completion of the intervention, 15–20 FCs and all HPs will be purposively selected from the two study sites for in-depth individual and focus group interviews.

### The intervention

The main thrust of the intervention is to provide support to the FCs by HPs through the interactive mobile app. The intervention will be implemented through the app over an 8-week period.

On receiving informed consent from the FCs, the selected HPs will approach them in their respective areas to download the mobile app on their smart phones or tablets (See Fig. 1). The following **functions** of the complex intervention will be conducted through the mobile app:
**Baseline health assessments** will be conducted via the mobile app. For baseline assessment, the FCs will be requested to go through the health assessment tools by answering questions in the app right after they download the app.**Interaction with HP**: FCs will be able to communicate directly with the HP through the app on a one-on-one basis. In addition, the HP will use a predetermined protocol to moderate group discussions on a weekly basis among a group of FCs.**Peer support:** During the 8-week period, the FCs will be able to communicate with their peers, i.e. other FCs of PWD, at the time of their preference.

**Fig. 1 Fig1:**
[figure not shown]
Care of Family Caregivers of Persons with Dementia (CaFCa): Research Plan

The above functions can be conducted through the following **features** of the mobile app:
***Health assessment tool*****:** FCs will be able to conduct self-assessments of stress, depressive symptoms, loneliness, quality of life and self-rated health. All data from the app will be secure and accessed solely by the research team.***Chat*****:** FCs will be able to communicate with other FCs for peer support and directly with HPs via the app, exchanging information and ideas on how to address the challenges in caring for a PWD, and where FCs can get support in their neighborhood.***Diary*****:** FCs document any events that may be stressful or upsetting for them, such as behavioral changes in the PWD and the FCs’ responses in order to seek support from the HPs.***Mindfulness:*** Mindfulness exercises will be available on the app for the FCs.***Notifications*****:** The HPs can share relevant information and events with the FCs.

The HPs will be trained by members of the research team including nurses with expertise in care of older persons and a psychologist to implement the intervention. The themes of the weekly group discussions are identified based on the findings of the qualitative interviews with FCs and HPs. These include physical and behavioral changes in dementia such as personality changes, progression of the disease, pain; importance of the FCs taking time for themselves e.g. for leisure activities, rest and sleep; complexity of feelings as a family member of a PWD, e.g. grief, shame, love; change in role from a partner or a child or a close relative of the PWD to a caregiver; financial and legal matters related to dementia care; and exploring the way forward.

Moderated by the research team, the HPs will meet twice during the intervention period to discuss and calibrate their approach to the group discussions, and to discuss challenges in leading the discussions. This will enhance fidelity of the intervention.

### Data collection

The *quantitative data* will be collected through the mobile app to capture the impact of the intervention implemented by HPs in alleviating stress, depressive symptoms and loneliness, and improving quality of life of the FCs.

The intended health related outcomes of the intervention study are presented in Table 1. Background information of the FCs such as demographic and living arrangement of the PWD cared for will be included. Outcomes will be measured via ***Health Assessment Tool*** in the app at baseline (T1) and three post-intervention time-points: right after the completion of the 8-week intervention (T2), 4 weeks (T3) and 8 weeks (T4) after the intervention (See Fig. 1).

**Table 1 Tab1:** Measurement of the primary and secondary outcomes in the intervention study

Primary outcome	Measurement
Caregiver stress	For caregivers of PWD: Zarit Burden Interview (12 items) [25]
Secondary outcomes	
Depressive symptoms	Patient Health Questionnaire (PHQ-9, 9 items) [26]
Loneliness	Single item question on loneliness [27]
Quality of Life	CarerQol-7D (7 dimensions) [28]

*In-depth interviews* with FCs will be conducted to get an understanding of their experiences of using the mobile app, peer support amongst the FCs and support from the HPs. The HPs will be interviewed to evaluate the implementation of the mobile app in terms of use and practicality of the app, and particularly in combination to their regular responsibilities. The interviews will be undertaken using a semi-structured interview guide and take place shortly after the 8-week intervention (T2).

Usage of the app will be assessed by analytics information, logged on backend system, on each of the features of the app mentioned above.

The usability of the intervention will be assessed by the following parameters:
Compliance of the usage of the app as indicated below (Derived from App data).
Use of health assessment tools.Reporting of stressful events.Frequency of communication between FC and the HP.Frequency of communication between FCs (Peer support).Participation of FCs in the weekly group discussions moderated by the HP.Use of mindfulness exercises.User Experience in terms of satisfaction level of the app interface and the content of the intervention (Interviews with FCs and HPs).User Experience in terms of ease of usage of the mobile app (Interviews with FCs and HPs).

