#### Quantitative

Sample size calculation of FCs is based on the primary outcome Caregiver’s Stress assessed by Zarit Burden Interview [25]. Assuming an effect size of 0.40, alpha .05, power 0.80, and 50% refusal or drop-out rate, the required sample size will be 78 FCs. In each study site, municipalities with HPs will be listed. HPs (approximately 5) at the randomly selected municipalities will be invited to participate in the study. FCs will be identified from the network of HPs that they provide support to for dementia care. The HPs will be responsible for coordinating 8–10 FCs in a group. If a HP provides support to more than 10 FCs, FCs will be randomly selected. Those not selected will continue to receive the standard support.

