The SPIRIT guidelines [31] was followed to structure the study protocol (https://www.spirit-statement.org/about-spirit/). One of the strengths of this intervention study is the inclusion of qualitative interviews with HPs specialized in dementia care and FCs form the groundwork of the development of the mobile app which is the central tool of the intervention study. Both stakeholders identified common issues to be addressed through the intervention as support to FCs. A limitation of the study is that the nature of the intervention tool excludes FCs of PWD who are not comfortable in using mobile technology. Even for those who are regular users of smart phones, writing messages in a chat function to participate in discussions with HP and peers may be challenging. The proposed mobile app has a core that is the same for all but can be modified to provide similar support to other FCs providing care to persons with chronic conditions.

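### Every outcome score is collected through the app that is itself the intervention, with no back-up route described, so missing outcomes are likely tied to disengagement

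*Protocol article*

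**What the plan says.** **Collection route.** Under Data collection, the quantitative data "will be collected through the mobile app to capture the impact of the intervention implemented by HPs". Outcomes are measured with the Health Assessment Tool "in the app at baseline (T1) and three post-intervention time-points": the end of the 8 weeks (T2), then 4 weeks (T3) and 8 weeks (T4) later. The intervention section says of the first set of scores that they "will be conducted via the mobile app. For baseline assessment, the FCs will be requested to go through the health assessment tools". This takes place directly after download.

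**Delivery route.** The same section says: "The intervention will be implemented through the app over an 8-week period".

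**Overlap of the two.** Data collection lists "Use of health assessment tools" among the parameters of compliance with the app. Filling in the outcome questionnaire therefore also counts as adherence.

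**Expected losses.** Sampling, Quantitative, plans 78 family caregivers (FCs): "Assuming an effect size of 0.40, alpha .05, power 0.80", with a "50% refusal or drop-out rate". Refusal and drop-out are not separated.

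**Comparison.** Data analysis compares baseline with post-intervention values in one group. FCs who are not selected keep standard support, but no outcome measurement is described for them. The only data described outside the app are the qualitative interviews, which give no outcome scores.

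**The concern.** When one tool both delivers the treatment and measures its effect, losing interest in the treatment and failing to supply outcomes tend to happen together. An FC who finds the app of little use, or has no time for it, is less likely to open it for the T2, T3 or T4 questionnaire. If staying is related to how burden changes, the mean change among responders differs from the mean change in all FCs who started.

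In a controlled trial, similar losses in both arms would offset part of this. Here nothing does, because the effect estimate is the single-group change itself. The planned association between logged use and outcomes is exposed to the same problem, since outcomes are seen mainly in FCs who still open the app. Scores not collected at T2 to T4 cannot be recovered later, and no analysis fully repairs informative loss.

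**Working it through.** **1. Inputs from the article.** Effect size 0.40 (type not stated), alpha 0.05 (sidedness not stated), power 0.80, 50% refusal or drop-out combined, N = 78, one group measured before and after.

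**2. Reproducing 78.** For a within-person change, the normal approximation is n = ((z_alpha + z_power) / 0.40)². Two routes give exactly 78:
- One-sided, normal approximation: ((1.645 + 0.842) / 0.40)² = 38.7, so 39; 39 / (1 − 0.5) = 78.
- Two-sided paired t-test (noncentral t): n = 52; 52 × 1.5 = 78.

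The article does not say which was used. Neither route shows how much of the 50% falls after baseline.

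**3. What the 50% can mean for 78 enrolled FCs.** If all of it is loss after T1, 39 give follow-up data, and power at 0.40 is 0.68 (two-sided paired t) or 0.79 (one-sided). If all of it is refusal before enrolment, 78 are followed and two-sided power is 0.94. Only loss after T1 can bias a within-person change; refusal before T1 affects whom the result applies to.

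**4. Illustration of selective loss (assumptions, not figures from the article).** The true mean change is zero. Staying depends on a latent normal tendency whose correlation with improvement is rho. A share p stays. Let c be the standard normal quantile at 1 − p, and lambda = phi(c) / p. Then:
- apparent change among responders = rho × lambda, in SD of the change;
- responders' SD = sqrt(1 − rho² × lambda × (lambda − c));
- false-positive rate = rejection probability of a two-sided 5% paired t-test at the ratio of these two, with n = 78 × p rounded down.

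Values of lambda: 0.3989 / 0.50 = 0.798 at 50% loss; 0.3178 / 0.75 = 0.424 at 25% loss; 0.1755 / 0.90 = 0.195 at 10% loss.

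| Loss after T1 | n | rho 0 | rho 0.1 | rho 0.2 | rho 0.3 |
|---|---|---|---|---|---|
| 50% | 39 | 0; 5% | 0.08 SD; 8% | 0.16 SD; 17% | 0.24 SD; 32% |
| 25% | 58 | 0; 5% | 0.04 SD; 6% | 0.08 SD; 10% | 0.13 SD; 16% |
| 10% | 70 | 0; 5% | 0.02 SD; 5% | 0.04 SD; 6% | 0.06 SD; 8% |

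Worked cell: 50% loss and rho 0.3 give 0.3 × 0.798 = 0.24 SD. If the planning effect of 0.40 is also in SD of the change, that is 0.24 / 0.40 = 60% of it.

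**5. Reading the table.** The large figures need both heavy loss after T1 and a moderate link between staying and improving. With no such link there is no bias at any loss. A negative rho gives the same sizes with the sign reversed, so that the app would look worse.

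**The case against.** Several stronger readings are tempting, and the article does not support them.

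- **That half the FCs are expected to drop out.** The 50% is a combined allowance for refusal and drop-out. Loss after T1 may lie anywhere from 0 to 50%, so the top row of the table is an extreme.
- **That leaving the intervention means leaving the study, so that only engaged users are analysed.** The Health Assessment Tool is a separate feature from chat, diary and mindfulness. An FC can ignore those and still answer the questionnaires, and T3 and T4 fall after the intervention has ended. *Mainly* engaged users is as far as one can go.
- **That the bias favours the app.** No section says who drops out. FCs whose caring role has ended or eased might also stop, which would remove improvers. Loss of those most burdened at baseline could remove the FCs most likely to regress downward.
- **That the article admits the problem.** The Discussion's remark that "writing messages in a chat function to participate in discussions with HP and peers may be challenging" concerns chat, not completing a questionnaire.
- **That the analysis mishandles missing data.** Which FCs enter the comparison, how missing scores are treated and which sensitivity analyses are run commonly belong in a statistical analysis plan, which is not at hand. Reminders may likewise be in the full protocol.

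All of these objections stand and limit the point. They do not remove it. The article states the collection route positively and repeatedly, and that route is also the treatment. This is a stated design feature, not a detail left for another document.

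**Conclusion.** The point holds as a cheap improvement to the design. Outcome collection shares its only described route with the intervention, in a single-group comparison with no control outcomes, so missing scores are likely tied to disengagement and the estimated change may mainly describe FCs who stayed engaged.

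The size is not derivable from the documents. Over the assumed range (no true effect, correlation 0.1 to 0.3, two-sided 5% paired test), the apparent change runs from 0.02 SD at 10% loss to 0.24 SD at 50% loss, and false positives from about 5% to 32%. The result rests on three things that the article does not give: the share lost after T1, the strength and sign of the link between staying and improving, and the sidedness of the test. It shows that the risk can matter, not that it will.

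**What to change.** In Data collection, keep the app as the primary route and add a back-up. At T2, T3 and T4, offer at least the 12-item Zarit Burden Interview by web link, SMS, post or telephone to every consented FC who has not completed it in the app, including those who have stopped using the app. Record the mode of completion for each assessment.

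The cost is keeping contact details, preparing a short form and following up non-responders among 78 FCs, which is minor administrative work. The drawback is possible differences between modes of completion, which the recorded mode allows the analysis to examine.

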### Data analysis

The *quantitative* data will be analyzed to describe and compare differences of means and standard deviations in stress, depressive symptoms, loneliness and quality of life amongst FCs between the baseline and post-intervention phases. ANOVA will be used to identify characteristics of FCs that are associated with the outcomes. Impact of the intervention on the probability of improving the outcomes specified in Table 1 will be assessed by regression analysis. All data will be entered and analyzed using Statistical Package for Social Scientists.

The *qualitative* data will consist of transcripts from the in-depth interviews with FCs and HPs. Using content analysis [29], the qualitative data will be analyzed to explore FCs’ experience of the use of the app. HPs’ experiences will be analyzed in terms of ease of use and practicality of the app as well as its integration in the standard care that they provide.

The *logged* data on the mobile app will be quantitatively analyzed for associations between use of the mobile app and the outcome measures.

The core research group will have access to the full data set. Other members of the research team will be provided sub-sets of data relevant for their respective studies.

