**Methods:**

Using a pragmatic intervention design, this study will use pre- and post-intervention assessment to evaluate the effectiveness of the proposed intervention in a sample of 78 FCs of persons with dementia (PWD). The intervention will be implemented by approximately 5 HPs specialized in dementia care based in the municipalities in Sweden. The main thrust of the intervention is to provide professional support, with help of an interactive mobile app, to family members in their caregiving role for PWDs. Qualitative interviews with HPs and FCs form the groundwork of the development of the mobile app. By using the app on smart phone or tablet, the FC, in groups of 8–10, will communicate with peers and a HP exchanging ideas on how to deal with PWD’s behavioral and cognitive changes and get support. They will also be able to discuss stressful events and access mindfulness exercises focused on themselves. Quantitative data will be collected before and at three time points after the 8-week intervention to assess changes in the health outcomes of the FCs. In-depth interviews will be conducted after the intervention to capture the experiences of FCs and HPs regarding the ease of use and acceptability of the app.

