### Secondary outcome

Reduction of depressive symptoms amongst family caregivers of persons of dementia.Reduction of loneliness amongst family caregivers of persons with dementia.Improvement of quality of life of family caregivers of persons of dementia.

A pragmatic intervention design will be used with pre- and post-intervention assessments. The pragmatic elements assess the intervention in a real-time environment, ensuring best possible applicability and generalizability into the context in which the study takes place. The intervention is individualized according to the needs of family caregivers and not a fixed intervention that is the same for all. It also provides evidence for recommendations of further implementation of the study once the research has been evaluated [22–24].

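### The 78 family caregivers at 80% power assume independent observations, although caregivers are treated in moderated peer groups under about 5 professionals and the named analyses carry no group term

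*Protocol article*

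**What the plan says.** The Abstract (Methods) has about 5 HPs delivering the intervention to 78 FCs, who, "in groups of 8–10, will communicate with peers and a HP". The Sampling section (Quantitative) adds: "The HPs will be responsible for coordinating 8–10 FCs in a group". It also says that FCs come from the network each HP already supports, and that an HP with more than 10 FCs has a random selection drawn. Under The intervention, "the HP will use a predetermined protocol to moderate group discussions on a weekly basis among a group of FCs", and FCs can chat with peers throughout the 8 weeks.

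The sample size statement is: "Assuming an effect size of 0.40, alpha .05, power 0.80, and 50% refusal or drop-out rate, the required sample size will be 78 FCs". It gives no ICC, design effect or number of groups.

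The design has one arm: "A pragmatic intervention design will be used with pre- and post-intervention assessments". The Data analysis section will "compare differences of means and standard deviations in stress, depressive symptoms, loneliness and quality of life amongst FCs between the baseline and post-intervention phases". It then names ANOVA for FC characteristics, regression for the effect on the probability of improvement, and associations between app use and outcomes. HP and group are not mentioned in any of these.

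**The concern.** FCs in one group share a moderator, a set of peers and a municipality, and that sharing is how the intervention is meant to work. The protocol also foresees that HPs may differ, because it has them meet twice to align how they lead discussions. A positive correlation of pre-post change within groups is therefore plausible.

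If it exists, the mean change is less precise than a calculation over independent FCs suggests. The stated power is then too high, and a test that ignores the groups rejects a true null too often. The study has no control arm, so the mean pre-post change in caregiver stress is its main evidence of effectiveness. The standard error of that change needs to be right.

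**Working it through.** **Inputs.** From Sampling (Quantitative): effect size d = 0.40, alpha 0.05, power 0.80, 50% refusal or drop-out, N = 78, groups of 8–10. From the Abstract: about 5 HPs. Assumed: d is the standardised pre-post change (there is one arm and the protocol does not say). Sidedness is not stated, so both are tried. ICC of the change is taken as 0.01 to 0.10, since none is given.

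**Reproducing 78.** One-sample or paired mean, independent FCs:
- One-sided, normal approximation: ((1.645 + 0.842) / 0.40)² = 38.6, so 39; 39 / (1 − 0.5) = 78.
- Two-sided, noncentral t: the smallest n reaching 80% is 52 (power 0.808); 52 × 1.5 = 78.

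Other variants miss 78. Two-sided normal gives 50 (100 or 75 after inflation), one-sided t gives 41 (82 or 62), and two-sample versions give 156 to 198 before drop-out. Both routes that reach 78 use a design effect of 1, so no clustering allowance is hidden in the figure.

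**Number of groups.** 5 × 8 = 40 and 5 × 10 = 50, short of 78. Conversely 78 / 10 = 7.8 and 78 / 8 = 9.75, so 78 FCs need about 8–10 groups, or 78 / 5 = 15.6 FCs per HP. Both 5 and 9 groups are therefore shown.

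**Power with clustering.** DE = 1 + (m − 1) × ICC, with m = completers / groups. Noncentrality = 0.40 × √(n / DE). Power is from the noncentral t with n − 1 df, or with (groups − 1) df for a group-level test. Example: 52 completers in 5 groups, m = 10.4, ICC 0.05: DE = 1 + 9.4 × 0.05 = 1.47; noncentrality = 0.40 × √(52 / 1.47) = 2.38; power 65% with 51 df, 44% with 4 df.

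| Setting | ICC 0.01 | 0.02 | 0.05 | 0.10 |
|---|---|---|---|---|
| DE, 52 in 5 groups | 1.09 | 1.19 | 1.47 | 1.94 |
| Power, two-sided, 51 df | 77% | 74% | 65% | 53% |
| Power, two-sided, 4 df | 55% | 52% | 44% | 36% |
| DE, 39 in 5 groups | 1.07 | 1.14 | 1.34 | 1.68 |
| Power, one-sided, 38 df | 77% | 74% | 68% | 60% |
| Power, one-sided, 4 df | 64% | 61% | 56% | 48% |
| DE, 52 in 9 groups | 1.05 | 1.10 | 1.24 | 1.48 |
| Power, two-sided, 51 df | 79% | 77% | 72% | 64% |

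The n − 1 df rows show the loss from correlation alone. The 4 df rows add the penalty for having few groups, which applies even at ICC 0: with 52 completers, noncentrality 0.40 × √52 = 2.88 and 4 df, two-sided power is 59%.

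**Type I error if groups are ignored.** For a two-sided 5% t-test, 2 × P(t > t₀.₉₇₅ / √DE) with n − 1 df gives 6 / 7 / 9 / 13% (39 in 5 groups) and 6 / 7 / 10 / 16% (52 in 5 groups) across the same ICCs. Simulation with 5 groups of 8 and 5 groups of 10 (40,000 runs each) agrees: 5.7 / 6.6 / 9.3 / 13.2% and 6.0 / 6.7 / 10.2 / 15.3%.

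**The case against.** The Data analysis section is a short summary in a journal article. It does not say that FCs are independent, and it leaves the form of the regression open. A full protocol or SAP could contain a group effect. This stands: a reader might infer that the trial will be analysed as if FCs were independent, but the text shows only that the analyses it names mention no such term. The objection does not reach the sample size. Its inputs are listed in full, 78 follows from them with a design effect of 1, and a later SAP could correct the standard errors but not restore the power.

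The ICC is assumed. The outcome is a within-person change, so stable differences between HPs or municipalities cancel. A common moderation protocol and the alignment meetings may also keep the ICC low. At ICC 0.01 with n − 1 df, the loss is only 2–4 points. This also stands and limits the size of the claim, not its direction.

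A reader might also conclude that true power is around 43 / 38 / 32% at ICC 0.02 / 0.05 / 0.10, from 39 completers, a two-sided test and 4 df. The documents do not support that as the effect of clustering. It pairs the completers of the one-sided route with a two-sided test. With no correlation at all, that pairing already gives 68% (38 df) or 48% (4 df). Much of the fall therefore comes from how drop-out is inflated and from the few degrees of freedom.

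Finally, about 5 groups is not certain, because 78 FCs imply 8–10 groups and the Timeline describes phased delivery. With 9 groups the loss is smaller but remains. If HPs lead successive groups, those groups are still nested in about 5 HPs, and the 9-group figures assume no correlation across groups of one HP.

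**Conclusion.** The concern holds for the power statement: 78 FCs give the stated power only if changes are uncorrelated within groups, and power falls short of 80% at every positive ICC tried, on either route that yields 78. With 5 groups and n − 1 df, the shortfall runs from about 3 points at ICC 0.01 to 20–27 points at ICC 0.10. It is larger if the test rests on group-level degrees of freedom.

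For the analysis, the supported statement is narrower: no HP or group term is named, and a test without one would be anti-conservative to the degree shown.

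The size rests on the assumed ICC, on reading 0.40 as a standardised change, and on an unclear number of groups. This should be fixed, but the documents do not show that it invalidates the study. Whether the 50% refusal or drop-out allowance was inflated correctly is a separate question.

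**What to change.** In Sampling (Quantitative), reconcile the number of groups with about 5 HPs, 8–10 FCs per group and 78 FCs. State whether HPs lead more than one group. State the sidedness, the number of completers and an ICC range, and give the resulting power with a design effect. This does not necessarily mean enrolling more FCs; an honest lower power for the feasible number is acceptable.

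In Data analysis, analyse the pre-post change with a random effect for HP/group (with repeated time points, on the change over time) and small-sample degrees of freedom (Satterthwaite or Kenward-Roger), or test the group mean changes directly. Carry the same term into the ANOVA and the app-usage analyses. If a SAP already does this, one sentence in the protocol pointing to it is enough.

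The cost is a change of wording, wider intervals and a less favourable stated power. No change to the intervention or data collection is needed beyond recording each FC's group and HP.

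### The regression for the impact of the intervention on the probability of improving has no intervention contrast, because every caregiver with outcome data receives the app

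*Protocol article*

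**What the plan says.** Protocol article, Secondary outcome section: "A pragmatic intervention design will be used with pre- and post-intervention assessments". No control arm is described.

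Sampling, Quantitative: "Sample size calculation of FCs is based on the primary outcome Caregiver’s Stress assessed by Zarit Burden Interview". The inputs are a standardised effect of 0.40, alpha 0.05, power 0.80 and 50% refusal or drop-out, giving 78 FCs. Where a healthcare professional (HP) supports more than 10 FCs, some are chosen at random: "Those not selected will continue to receive the standard support". No outcome measurement is described for the unselected FCs.

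Data collection: outcomes come from the assessment tool inside the app, at baseline (T1) and then "right after the completion of the 8-week intervention (T2), 4 weeks (T3) and 8 weeks (T4) after the intervention".

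Data analysis lists four quantitative elements:
- The first is to "describe and compare differences of means and standard deviations in stress, depressive symptoms, loneliness and quality of life" between baseline and the post-intervention phases.
- ANOVA is used to relate FC characteristics to outcomes.
- The third is the sentence at issue: "Impact of the intervention on the probability of improving the outcomes specified in Table 1 will be assessed by regression analysis".
- Logged app use is examined for association with outcomes.

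None of the four is named as primary.

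**The concern.** A regression that estimates the impact of an intervention needs rows that differ in exposure. *Improving* is a change relative to T1, so it exists only at T2, T3 and T4, and by then every FC supplying data has been given the app. No term in such a model can stand for the intervention.

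This sentence is the only one in the section that uses the word *impact*, and the study's stated aim is to assess effectiveness. A reader of the results could take a proportion improved, or an odds ratio for a covariate, as the effect of the app. If improvement means any decrease and changes are symmetric without ties, about half of the FCs would improve even with no effect. The sentence also implies a binary outcome, while the sample size was set for a standardised effect on a score.

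**Working it through.** **1. The plan's own figure.** 78 is reproduced as a one-group mean-change calculation with d = 0.40, in either of two ways:
- Two-sided alpha 0.05, noncentral t: n = 52, and 52 × 1.5 = 78.
- One-sided alpha 0.05, normal approximation: ((1.645 + 0.842)/0.40)² = 38.7, rounded up to 39, and 39/(1 − 0.5) = 78.

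A two-group comparison at d = 0.40 would need 198 in total (156 one-sided) before drop-out. So 78 fits a within-person mean change, taking 0.40 as mean change divided by its SD. The article does not state sidedness, so both 52 and 39 completers are carried forward.

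**2. Is there an intervention contrast?**
- One row per FC, outcome improved yes/no, columns intercept and intervention: both columns are all ones, so the rank is 1 of 2 and the intervention coefficient is not identifiable.
- Stacking T2, T3 and T4 gives up to three rows per FC. Every row is still exposed, so the rank stays at 1.
- Baseline and post-intervention rows with a pre/post term give rank 2. The outcome must then be a status or score at each visit. It cannot be *improved*, which has no value at T1.

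The choice of link, cut-off or covariates does not change the first two results.

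**3. Power if the binary analysis were the effectiveness test.** Assumptions: changes are normal with d = 0.40, any decrease counts as improvement, and there are no ties. Then P(improve) = Φ(0.40) = 0.655, against 0.50 under no effect.

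The paired t-test uses the noncentral t with n − 1 degrees of freedom and noncentrality 0.40√n. The exact sign test rejects, in the upper tail, at 34 or more of 52 (two-sided size 2 × 0.0182 = 0.036) or 27 or more of 39 (2 × 0.0119 = 0.024). The normal approximation is Φ{[(p − 0.5)√n − z × 0.5]/√(p(1 − p))}, with z = 1.96 two-sided or 1.645 one-sided.

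| Completers | Sides | Paired t | Sign test, exact | Sign test, approx. |
|---|---|---|---|---|
| 52 | 2 | 80.8% | 57.3% | 61.6% |
| 39 | 2 | 68.2% | 38.2% | 49.2% |
| 39 | 1 | 79.1% | 51.5% | 62.2% |

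At n = 39 two-sided the gap is 68.2 − 38.2 = 30 points. About 49.2 − 38.2 = 11 of these come from discreteness. The next rejection boundary (26 of 39) has size 2 × 0.0266 = 0.053 and power 51.5%.

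For 80% two-sided power the binary analysis needs, by the approximation, [(1.96 × 0.5 + 0.842 × 0.475)/0.155]² ≈ 79 completers, against 52 for the mean change.

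**The case against.** The strongest reply is that the article gives no model form, and a condensed article may leave that to a fuller plan. In a pre/post design, a repeated-measures regression of status or score on phase would be estimable, though confounded with time, and the text does not exclude it. It remains true that such a model has a different outcome from the one written. What the sentence commits to is an effect on the probability of improving, and later detail cannot supply the missing contrast. The planned analysis of app use does have varying exposure, but it is listed separately. It compares heavier with lighter users, not the intervention with its absence.

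Three stronger readings are tempting, and the document does not support them.
- **That no effect estimate is planned at all.** The comparison of baseline and post-intervention means is planned in the same section and is the natural estimate for this design.
- **That the sample size fails, or that power has been discarded.** 78 fits the mean comparison, which is kept. Power is lost only if the regression is the effectiveness test, and the article does not say that it is.
- **That 38% against 68% is the size of the loss.** The plan names neither a sign test nor an any-decrease cut-off, and part of the gap is discreteness. Unchanged scores are possible on a 12-item scale, so the proportion improved under no effect could also be below one half.

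It is also fair to object that a mixed model in the same sample has no unexposed comparison either. That stands, and the replacement wording must say so.

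**Conclusion.** The concern holds for the regression sentence. As written it promises an intervention effect that the described design cannot identify, because improvement is defined only after baseline and all FCs with outcome data receive the app. This conclusion needs no distributional assumption.

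The power loss is conditional. It applies only if the regression is the effectiveness test, with normal changes at d = 0.40 and any decrease as the cut-off. Two-sided power then falls from about 81% to 57% at 52 completers, or from 68% to 38% at 39. On the normal approximation the binary figures are 62% and 49%, and another cut-off would change them. The planned comparison of means and the figure of 78 are not undermined by this point.

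**What to change.** Replace the sentence with a repeated-measures linear mixed model of the continuous 12-item Zarit score at T1 to T4:
- Fit time as a categorical effect with a random intercept for FC. Account for HP group as far as about 5 groups allow, since a variance component on so few is weakly estimable.
- Name change from T1, with its 95% CI, as the main effectiveness estimate, and describe it as uncontrolled within-person change.
- Use the same model for PHQ-9 and CarerQol-7D, and an ordinal or other suitable repeated-measures model for the single loneliness item.
- Keep the proportion improved as a descriptive summary only, without the word *impact*.
- Include a group-by-time comparison with unselected FCs only if their outcomes are actually measured. The present plan does not collect them.

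The cost is a change of wording, slightly more analysis work and a more modest causal claim. No new data are needed.
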